# Evaluation on the effect of acupuncture on patients with sepsis-induced myopathy (ACU-SIM pilot study)

**DOI:** 10.1097/MD.0000000000020233

**Published:** 2020-05-22

**Keywords:** acupuncture, muscle wasting, pragmatic controlled trial, sepsis

## Abstract

**Background::**

Sepsis-induced myopathy (SIM) is a disease that causes motor dysfunction in patients with sepsis. There is currently no targeted treatment for this disease. Acupuncture has shown considerable efficacy in the treatment of sepsis and muscle weakness. Therefore, our research aims to explore the effects of acupuncture on the improvement of muscle structure and function in SIM patients and on activities of daily living.

**Methods::**

The ACU-SIM pilot study is a single-center, propensity-score stratified, assessor-blinded, prospective pragmatic controlled trial (pCT) with a 1-year follow-up period. This study will be deployed in a multi-professional critical care department at a tertiary teaching hospital in Guangzhou, China. Ninety-eight intensive care unit subjects will be recruited and assigned to either the control group or the acupuncture group. Both groups will receive basic treatment for sepsis, and the acupuncture group will additionally receive acupuncture treatment. The primary outcomes will be the rectus femoris cross-sectional area, the Medical Research Council sum-score and time-to-event (defined as all-cause mortality or unplanned readmission to the intensive care unit due to invasive ventilation). The activities of daily living will be accessed by the motor item of the Functional Independence Measure. Recruitment will last for 2 years, and each patient will have a 1-year follow-up after the intervention.

**Discussion::**

There is currently no research on the therapeutic effects of acupuncture on SIM. The results of this study may contribute to new knowledge regarding early muscle atrophy and the treatment effect of acupuncture in SIM patients, and the results may also direct new approaches and interventions in these patients. This trial will serve as a pilot study for an upcoming multicenter real-world study.

**Trial registration::**

Chinese Clinical Trials Registry: ChiCTR-1900026308, registered on September 29th, 2019.

## Introduction

1

Rapid muscle wasting is commonly seen in septic patients during their very first days within the intensive care unit (ICU).^[1,2]^ This phenomenon has been described as sepsis-induced myopathy (SIM),^[3,4]^ one of the most vital components of ICU-acquired weakness.^[4]^ This persistent situation is more common in skeletal muscles and respiratory muscle groups.^[5,6]^ If left untreated, or even the intervention is just delayed, SIM could last for years in survivors of sepsis. SIM can lead to prolonged mechanical ventilation, long-lasting limb motor dysfunction, a protracted in-hospital stay, unplanned readmission and increased long-term mortality.^[7,8]^

At present, there is no targeted treatment for SIM. The efficacy of early rehabilitation (such as in-bed passive/active leg cycling therapy) remains controversial.^[2,9]^ Initiation of these kinds of intervention has barriers in the real world (ie, lack of facilities, personnel and equipment, or the patient cannot fully cooperate with the muscle group exercises).^[10]^ In addition, septic patients may need central venous catheterization and/or invasive arterial monitoring (A-line), not to mention the needs of those who received Intra-aortic balloon pump or extracorporeal membrane oxygenation. All of these factors lead to difficulties in conducting early physical therapy in septic patients. Hence, the development of an easy-to-perform, SIM-targeted treatment is of paramount importance for improving muscle wasting in patients with sepsis.

Acupuncture has been shown to have some advantages in patients with sepsis or muscular diseases separately. However, to the best of our knowledge, no study of acupuncture has been performed or is ongoing in patients with sepsis combined with muscle wasting.

First, several animal experiments have confirmed that acupuncture can improve sepsis by regulating inflammation. Scognamillo-SzabÓ and his colleagues reported that acupuncture can reduce the degree of inflammation during sepsis and effectively curb the development of sepsis.^[11]^ In an LPS-stimulated rat model, pretreatment with acupuncture at ST36 (Zusanli) in septic mice reduced the degree of kidney damage by lowering iNOS levels.^[12]^ In addition, Song JG et al indicated that electroacupuncture preconditioning increased the survival rate by decreasing the pro-inflammatory cytokine concentration.^[13]^

Second, acupuncture has had therapeutic effects in the treatment of acute muscle wasting. Su and his teammates found that acupuncture was effective against skeletal muscle atrophy and promoted muscle regeneration in denervation-induced muscular atrophic mice.^[14]^ Suzuki et al revealed that acupuncture significantly improved grip strength and respiratory muscle strength in chronic obstructive pulmonary disease participates within a RCT.^[15]^ After 12 weeks of treatment, the improvements in the grip strength and respiratory muscle strength in the acupuncture group were significant when compared to those in the sham-acupuncture group. This indicates that acupuncture might have an effect on the improvement of muscle weakness.^[15]^ In addition, Takaoka et al found that acupuncture can alleviate muscle atrophy in rats by downregulating the gene expression of myostatin (MSTN) in an animal experiment.^[16]^

Electrical muscle stimulation (EMS) seems to be another candidate for treating muscle weakness. Several studies have already suggested that neuromuscular electrical stimulation might have potential benefits in a rat model of acute muscle atrophy.^[17,18]^ Furthermore, researchers conducted a clinical RCT that enrolled 140 ICU patients into two arms, 68 into the EMS arm and 72 into the control arm; daily EMS treatment was provided in the EMS arm. The results showed that the incidence of polyneuromyopathy, a critical illness, was lower in the EMS arm than in the control arm, indicating that conventional EMS can attenuating the development of muscle weakness in ICU patients.^[19]^ It is a pity that this trial was not specifically designed for septic patients. In summary, based on the results of the existing literature, a therapeutic effect of EMS on sepsis has not yet been shown.

There is currently no clinical evidence, either randomized controlled trials or real-world studies, for acupuncture treatment of SIM. Our group intends to analyze prospective data through real-world research methods and to explore the clinical effects of acupuncture on septic muscle atrophy to provide a basis for subsequent clinical research.

Based on the clinical instinct and the experience of our team, septic patients experienced acupuncture treatments during their ICU stays. We hope that this study will provide some references for the upcoming clinical trial.

### Research objectives

1.1

Acupuncture has already been deployed in the treatment of sepsis or muscle weakness. Nevertheless, its efficacy and safety in SIM remains unclear. Therefore, this study has the following research objectives:

(1)To describe the progression of loss of muscle mass (the change of rectus femoris cross-sectional area [RF_CSA]_ from baseline) in patients with sepsis after admission to the ICU and to investigate whether the decline in RF_CSA_ is the morphological basis for muscle weakness in septic patients.(2)To assess whether acupuncture at the Yang-Ming meridian acupoints affects the changes in RF_CSA_ and muscle strength and the long-term prognosis and safety in SIM simultaneously.(3)To serve as pilot research for an upcoming multicenter real-world study.

## Methods

2

### Design

2.1

The ACU-SIM pilot study is a single center, propensity-score stratified, assessor-blinded, prospective pragmatic controlled trial with a 1-year follow-up period. We hope to assess the therapeutic effect and safety of acupuncture on SIM patients.

### Setting

2.2

This study will be implemented in a 37-bed interdisciplinary critical care ward of a tertiary, academic, teaching hospital: the first affiliated hospital of Guangzhou University of Chinese Medicine, China. All diagnoses and treatments will be performed by trained physicians and technicians.

### Sample size

2.3

Temporarily, there are no data on how acupuncture benefits patients with SIM. Therefore, we searched for related studies. In the trial “Electrical muscle stimulation prevents critical illness polyneuromyopathy.”^[19]^ the incidence rates were 12.5% in the EMS group and 39.3% of the control group. Assuming α = 0.05 and 1-β = 0.8, and an experimental group to control group ratio of 1:1, the sample size was calculating by STATA software (STATA IC 15.0, Stata Corp, College Station, TX). We will need 39 patients in the experimental group and 39 patients in the control group. Considering factors such as dropouts, the sample size of the acupuncture group and the control group is designed to be 49 and 49, respectively; a total of 98 cases will be observed.

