### Statistical analysis

2.10

All available data will be analyzed descriptively. For continuous data, the normality test will be applied at the very beginning of the analysis. We will bewrite the results as the means, standard deviations, and 95% confidence intervals (CIs) for continuous data that conform to the normal distribution; medians, quartiles, and ranges for rank data and continuous data that do not fit the normal distribution; and percentages for discrete data.

The change in the RF_CSA_ from baseline will be analyzed by a generalized additive mixed model of repeated measures design. Analysis of the time-to-event outcome (at day 28, day 90, six months, and 1 year after the admission of ICU) will be conducted by applying Kaplan-Meier curves. Kaplan-Meier survival curves will be performed to describe the survival rate between the 2 groups, and the log-rank method will be used to compare the survival rates of the acupuncture group and control group. Multivariate Cox proportional hazard regression models will be used to analyze several constituents (such as acute physiology and chronic health evaluation-II, SOFA score, demographic and diagnostic data), adjust for covariates, and correct for confounding. Our team will use similar approach mentioned above to analyze secondary outcome measures when they can be expressed as time-to-event outcome dimensions. All regression analyses (generalized additive mixed models, log-rank analysis, multivariate Cox proportional hazard regression models) will include the same covariates as the primary analysis. If there are any measurable differences between the 2 study groups with regard to prognostic factors, a propensity score analysis will be applied to assess the sensitivity of the results to any treatment allocation biases. The propensity score will be set for the main outcome. After the 2 sets of data are analyzed according to the previous analysis, the patients will be matched with the propensity score, and then the main outcomes of the matched 2 groups will be compared again to see if there are any similarities or differences between the 2 groups before and after the match. If they are the same, the results are stable; however, a difference means that there are factors affecting the evaluation of the outcome before the match, and these factors will need to be explained.

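### The 80% power in section 2.3 is for polyneuromyopathy incidence at a single 5% test, so it applies to none of the three primary outcomes

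*Protocol article*

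**What the plan says.** Section 2.3 states that no data exist on acupuncture in sepsis-induced myopathy and turns to a related trial of EMS, where "the incidence rates were 12.5% in the EMS group and 39.3% of the control group". It continues: "Assuming α = 0.05 and 1-β = 0.8, and an experimental group to control group ratio of 1:1", and concludes: "We will need 39 patients in the experimental group and 39 patients in the control group". The allowance for losses follows: "Considering factors such as dropouts, the sample size of the acupuncture group and the control group is designed to be 49 and 49".

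The Introduction identifies what those rates measure: "The results showed that the incidence of polyneuromyopathy, a critical illness, was lower in the EMS arm than in the control arm". It also says that the EMS trial was not designed specifically for septic patients. The trial title cited in section 2.3 shows that its aim was prevention.

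The Abstract gives this trial's own outcomes: "The primary outcomes will be the rectus femoris cross-sectional area, the Medical Research Council sum-score and time-to-event". Section 2.8 repeats the same three. It adds the motor item of the FIM, and as secondary outcomes myostatin level, lengths of stay and ventilation duration. Section 2.10 plans a generalized additive mixed model for RF_CSA change, and Kaplan-Meier curves, log-rank and Cox models for time-to-event. It describes no comparison of a binary incidence.

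**The concern.** A power statement tells the reader what a trial of that size can detect on the outcome it will report. Here the quantity powered is a binary incidence from another population, while the outcomes reported are a repeated continuous area, a 0 to 60 score and a time to event. The text gives no step from one to the other. A reader who takes 80% power as describing the RF_CSA, MRC-SS or time-to-event result would be misled, and a null result on any of them could be given more weight than 98 patients support.

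The calculation also spends alpha 0.05 on one test while three outcomes are called primary. Whatever success rule is meant, a single pair of alpha 0.05 and power 0.8 does not describe three primary tests.

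**Working it through.** **1. The plan's own figure.** Inputs from section 2.3: p1 = 0.125, p2 = 0.393, alpha 0.05, power 0.80, ratio 1:1. Sidedness is not stated; two-sided is assumed.

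Unpooled formula: n = (1.960 + 0.842)² × [p1(1 − p1) + p2(1 − p2)] / (p2 − p1)².

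- Variance term: 0.1094 + 0.2386 = 0.3479
- Squared difference: 0.268² = 0.0718
- n = 7.849 × 0.3479 / 0.0718 = 38.02, so **39 per group**

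The pooled formula gives 41, and exact power of the Pearson test at 39 per group is 0.800. The dropout rate is not stated, but 39 / 0.80 = 48.75, so 49 per group and 98 in total imply about 20%. The stated numbers are therefore correct for the question they answer.

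**2. Does that question appear in the plan?**

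| Item | Where | Polyneuromyopathy incidence? |
|---|---|---|
| Primary outcomes | Abstract, 2.8 | No |
| FIM motor item | 2.8 | No |
| Secondary outcomes | 2.8 | No |
| Planned analyses | 2.10 | No analysis of a binary incidence |
| Nearest relative | 2.8.2 | MRC-SS below 48 defines weakness, but is not named as an outcome or tied to 2.3 |

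The source rates also carry some undisclosed uncertainty. The Introduction says that the EMS trial "enrolled 140 ICU patients into two arms, 68 into the EMS arm and 72 into the control arm". But 12.5% of 68 is 8.5 patients and 39.3% of 72 is 28.3, so the rates are not over the full arms. This is a side point.

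**3. One test against three primary outcomes.**

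- Any one suffices, independent tests: 1 − 0.95³ = 0.143. With a common correlation of 0.3, 0.5 or 0.8 (assumed), simulation gives 13.6%, 12.5% and 9.8%.
- All three must succeed: type I error stays within 5%. If each test had 80% power and the tests were independent, joint power would be 0.8³ = 0.51. Correlation raises this, but it cannot exceed the power of the weakest test.

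**4. What the size can detect on the listed kinds of outcome** (two-sided 5%, 80% power). The document gives no SD, event rate or target hazard ratio, so only detectable effects can be stated.

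- Continuous outcome at one time, two-sample comparison: the normal approximation (1.960 + 0.842) × √(2/n) gives 0.63 at n = 39 and 0.57 at n = 49. The t-test gives 0.64 and 0.57.
- Time-to-event: HR = exp(−2 × 2.80 / √E). With E = 30 events, 0.36; with E = 50, 0.45. Both event counts are assumed, for illustration only.

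**The case against.** The strongest reply is that the endpoint is not foreign. The Introduction reads the EMS trial as evidence on muscle weakness, section 2.4.4 uses MRC-SS to judge ICU-acquired weakness, and section 2.8.2 gives the cut-off of 48. MRC-SS is a primary outcome, so the size may have been meant for its dichotomised form. That is plausible and it shapes the fix. But the article never says so, and the listed outcome is the score.

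A second reply is that this is a pilot, open about borrowing its rates. That softens the consequence, but section 2.3 still claims formal power and section 2.10 plans comparative tests.

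A third is that a success rule may stand in a full protocol or SAP not shown. This is fair, so the absence of such a rule is not the point here. The point is that the published calculation covers one test.

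Four stronger readings are tempting, and the document does not support them:

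- **The false-positive risk is well above 5%.** This needs an any-of-three rule, which is not stated. Objective 2 in section 1.1 speaks of affecting muscle area, strength and prognosis simultaneously, which could mean that all must succeed. Objective 1 also expects area and strength to be related, so independence is an upper case.
- **The error reaches about 20% through four time-to-event tests.** Section 2.10 says "Analysis of the time-to-event outcome (at day 28, day 90, six months, and 1 year after the admission of ICU" in connection with Kaplan-Meier curves. Its log-rank sentence names no times, and those times are the follow-up visits, so four separate tests are not clearly planned.
- **Time-to-event is badly underpowered.** Without an event rate or target hazard ratio in the document, only conditional figures can be given.
- **A prevention rate cannot apply because everyone has already lost more than 9.24% of RF_CSA.** Entry requires loss of area, not weakness, which section 2.8.2 defines separately. Whether the rates carry over is uncertain, not excluded.

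**Conclusion.** The point holds as a mismatch between the power statement and the outcomes. The figures 39, 49 and 98 are not miscalculated. The 80% belongs to a two-proportion comparison that the plan neither lists nor analyses, and it applies to none of the three primary outcomes. This conclusion rests on the text alone. The multiplicity part is conditional: error of up to 14.3% if any one outcome suffices (independence assumed), or error within 5% with reduced joint power if all must succeed. The standardised differences of 0.64 and 0.57 assume a two-sample comparison at a fixed time and are only approximate for the mixed model planned for RF_CSA.

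**What to change.** Keep 98 patients and amend section 2.3, with matching words in 2.8 and 2.10, in one of two ways.

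- **(a)** Name ICU-acquired weakness (MRC-SS below 48) at a stated assessment, such as ICU discharge, as the outcome on which the size is based. Add a two-proportion analysis to 2.10, and say that 12.5% and 39.3% are borrowed from a different population.
- **(b)** Withdraw the 80% claim for 12.5% against 39.3%. State instead the difference detectable on a named primary outcome. For example, for a two-sample comparison of a continuous outcome at a fixed time, 39 evaluable per group give 80% power at two-sided 5% for a standardised difference of about 0.64 (0.57 with 49), approximate for the mixed-model analysis.

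In either case, state which primary outcome carries the 5% level and that the power statement does not cover the other two. Which outcome that is remains the investigators' choice. Any hazard ratio quoted for time-to-event should be labelled as resting on an assumed event count.

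The cost is wording only, with no extra patients. The price is a less favourable power claim that applies to one outcome.

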### Study procedures

2.4

#### Electronic data capture (EDC) System

2.4.1

The Department of Critical Care Medicine at the First Affiliated Hospital of Guangzhou University of Traditional Chinese Medicine has already deployed a cloud-based EDC system (website: https://study.empoweredc.com/site/203). Each patient will be assessed within 24 hours after ICU admission, and patients who meet the sepsis diagnosis will be entered into the system. Peripheral serum will be collected prospectively at baseline and at subsequent time points and will be stored in the biological sample bank (Ling-Nan Medical Research Center) to test MSTN expression levels. Patients who meet the SIM diagnosis will be marked in the EDC according to the diagnostic criteria. Two intensivists will measure the RF_CSA_ of the sepsis patients at the measurement time point and will then enter the data into the EDC system; a consistency evaluation will be performed. One ICU specialist and 1 neurologist will evaluate the medical research council sum-score (MRC-SS) of the SIM patients.

#### Participant eligibility

2.4.2

A total of 98 subjects will be recruited from our multidisciplinary ICU if they fulfill the inclusion criteria and do not have any exclusion criteria. Figure 1 shows the overview of the recruitment process.

**Figure 1 F1:**
[figure not shown]
Study flowchart.

#### Inclusion criteria

2.4.3

(1)Age 18 to 85 years old;(2)Met the criteria of Sepsis 3.0^[20]^, which defines sepsis as infection + sequential (sepsis) organ failure assessment score (SOFA) ≥ 2 points within the first 24 hours;(3)First ICU admission and the patient should be expected to survive within the first 48 hours;(4)Informed consent was signed by the patient or their next to kin;(5)The RF_CSA_ decreased more than 9.24%^[21]^ after ICU admission;(6)Alive during the ICU stay.

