#### Exclusion criteria^[1,2]^

2.4.4

(1)A confirmed pregnancy or the urine β-HCG test is positive;(2)The questionnaires (MRC-SS and FIM^TM^) or consent form could not be completed due to cognitive abnormalities.(3)A newly diagnosed primary neuromuscular disease when admitted to the hospital;(4)Leg amputation, pelvic/femoral fractures or knee/hip replacement that prevent the measurement of the RF_CSA_;(5)Malnutrition (BMI less than 18.5 kg/m^2^) or cachexia;(6)Metastatic tumors (PD) or ongoing chemotherapy;(7)Cardiorespiratory arrest or imminent death;(8)Long-term corticoid treatment;(9)Could not walk independently before sepsis onset;(10)ICU length of stay (LOS) < 7 days^[2]^;(11)Sepsis onset more than 5 days before ICU admission^[2]^;(12)Therapy withdrawal or consent refusal.

Patients are eligible if they are diagnosed with sepsis, their RF_CSA_ decreased more than 9.24%^[21]^ from baseline, and informed consent has already acquired from the patient and/or immediate family member. A case report form (CRF) will be completed, and the RF_CSA_, MRC-SS score and other relevant data will be obtained, for all eligible and consenting patients. We will use the RF_CSA_ to assess the changes in muscle morphometry; the MRC-SS will be used to assess whether patients meet the diagnostic criteria of ICU-acquired weakness and to observe mortality, rehospitalization, reintubation and mechanical ventilation and other relevant indicators during the 1-year follow-up.

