#### Acupuncture treatment

2.5.1

According to the patient's (and/or their relatives’) willingness and the clinical routine, a group of physicians will assess the acupuncture treatment within 24 hours in patients who meets the inclusion criteria 1 to 5. All physicians are required to have at least 3 years (or 300 hours) of practical experience with acupuncture. The acupuncture treatment will be performed by stainless steel needles (0.30 mm × 40 mm; 0.30 mm × 25 mm; Suzhou Medical Supplies Factory Co., Ltd., Suzhou City, China). The acupuncture treatment will be performed by the technique of lifting, thrusting, twirling and rotating the needle until the patient is being “De-qi” (getting a numbness or other acupuncture feeling). Two points that do not cross the joint will be chosen for electrical stimulation. The needle will be kept in place for approximately 30 minutes. By the time we remove the needles, a clean cotton balls will be pressed to the skin to prevent bleeding.

All patients must be treated at “3 obligatory basic acupuncture points”: ST36, ST40 and LI10. Furthermore, at least 3 additional acupuncture points will be selected according to the principles of traditional Chinese medicine (for example, if the patient has a mental disorder manifestation, acupoints such as GV20, GV24, and EX-HN3 can be added to promote the patient's waking). Additional acupoints could be applied, and ear acupuncture points might also be included. All acupoints selected in each session will be recorded. A traditional Chinese syndrome diagnosis is required, and the diagnosis will be documented. Acupuncture treatment will be performed twice a day and lasts for 30 minutes. If the included subjects do not meet the exclusion criteria and do not terminate their participation in study, they will receive acupuncture treatment during their entire ICU stay. If the patient is discharged from the ICU, the acupuncturist will continue to follow the patient until the 14-day acupuncture session is completed. Both the acupuncture group and the control group will receive basic sepsis treatment. The selection of acupuncture points is listed in Table 1.

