### Study groups

2.7

Since this study is a real-world study, the grouping of the study subjects was determined by the actual observations. Therefore, no randomization of groups was set in this study. The subjects will be as allocated into 2 arms.

Group 1: acupuncture group

When the participant meets the inclusion criteria (1 to 5), the acupuncturist will assess the conditions for patient treatment. Patients can enter this group and have acupuncture treatment if they do not have specific conditions (such as edema, coagulopathy, acupoints local skin and soft tissue infection, and rejection of acupuncture treatment) that are not suitable for acupuncture.

Group 2: control group

Patients who are not suitable for acupuncture or are not willing to receive acupuncture could enter this group. In addition to basic treatment, patients in this group will be prescribed exercises, such as early in-bed activities or wheelchair activities.

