### Outcome

2.8

The primary outcomes will be the decline of RF_CSA,_ the MRC-SS and time-to-event (defined as all-cause mortality or unplanned readmission to the ICU due to invasive ventilation). The activities of daily living will be accessed by the motor item of the Functional Independence Measure (FIM^TM^). Secondary outcome includes the expression level of MSTN, ICU length of stay, length of hospital stay, duration of invasive/non-invasive mechanical ventilation. The outcomes will be measure as follow:

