#### Collecting healthcare data within the ICU stay

2.8.6

During the screening period, the relevant subject information will be completed, and baseline demographic-related items will be collected. The SOFA score, the immediate acute physiology and chronic health evaluation II score (and SAPS score), the GCS score, body temperature, mechanical ventilation or not, the infection site, the pathogenic examination before the administration of antibiotics or use of vasoactive drugs, arterial blood gas analysis, blood routine, coagulation function, liver function, kidney function, heart function, infection index, urine pregnancy test (female subjects), and an electrocardiogram will be recorded during this period. The length of the first antibiotic use and whether the pathogen is sensitive to the antibiotic will be recorded after initiation.

For patients who survive and are discharged from the ICU - meeting all inclusion criteria (1 to 6) - the mechanical ventilation duration time, LOS, total hospital stay, sum sedative analgesic dose, statin dose, blood glucose level, insulin dosage, glucocorticoid dosage, protective constraints, and the duration of neuromuscular blockers will be additionally recorded.

Table 2 shows a general view of the data collecting and the time of acquisition for each item. We will manage all study data anonymously, and all CRFs will be labelled with a study number allocated to each individual participant. The CRF will be in both paper and electronic formats. The paper version of the CRF will be used for backup storage of data and for verification when needed. The daily management of data will be completed on the EDC system. And the details of bedside data collection are shown in Table 3.

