### Adverse events

2.13

In this study, adverse events will be defined as follow:

(1)Fainting: Fainting means that the patient suddenly developed dizziness, palpitation, nausea, and even syncope during the acupuncture process; fainting is common in the acupuncture process.(2)Broken needle: when the acupuncture needle breaks inside the patient.(3)Hematoma: swelling and pain caused by a subcutaneous hemorrhage at the acupuncture site during or after the needle puncture.(4)Bent needle: When the needle is inserted into the acupoint, the needle is bent in the body.(5)Sticking of the needle: After the needle is inserted, when lifting and twisting the needle or when the needle is pulled out, the needle feels very heavy, tight, and even twitching; the needle is difficult to twist or remove, and the patient feels pain abnormal.(6)Infection: infection at the acupuncture site after acupuncture.

If the above situations occur, they will be urgently handled by the acupuncturist and the ICU physician; if the researcher determines that the research plan does not needed to be adjusted, the research will continue. If the condition changes and the study treatment plan need to be stopped or changed, the subject will be withdrawn from the study and the events will be recorded in detail. All subsequent clinical treatments are based on the principle of saving the life of the subject and improving the prognosis of the disease. For all adverse events, the adverse event report form needs to be completed and the events need to be reported.

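### Acupuncture starts on inclusion criteria 1 to 5, but inclusion 6 later removes every death in the index ICU stay, while the primary mortality outcome is timed from ICU admission

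*Protocol article*

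**What the plan says.** All places are in the protocol article.

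- **Start of treatment and grouping.** Section 2.5.1: "a group of physicians will assess the acupuncture treatment within 24 hours in patients who meets the inclusion criteria 1 to 5". Section 2.7, on the acupuncture group: "When the participant meets the inclusion criteria (1 to 5), the acupuncturist will assess the conditions for patient treatment". Patients found unsuitable, or unwilling, go to the control group.
- **Inclusion 6.** Section 2.4.3 adds "Alive during the ICU stay". Section 2.8.6 shows when it applies: "For patients who survive and are discharged from the ICU - meeting all inclusion criteria (1 to 6". Section 2.4.2 says that the 98 subjects fulfil the inclusion criteria and have no exclusion criterion.
- **Exclusions 10 and 12.** Section 2.4.4 excludes "ICU length of stay (LOS) < 7 days" and "Therapy withdrawal or consent refusal". Section 2.5.1 makes continued treatment of included subjects depend on their still not meeting an exclusion criterion.
- **Primary time-to-event outcome.** Section 2.8: "defined as all-cause mortality or unplanned readmission to the ICU due to invasive ventilation". Section 2.10 reads it at day 28, day 90, six months and 1 year from ICU admission, with Kaplan-Meier, log-rank and Cox methods and a propensity-score sensitivity analysis.
- **Leaving the study.** Section 2.13: "If the condition changes and the study treatment plan need to be stopped or changed, the subject will be withdrawn from the study".

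**The concern.** Patients are treated on five criteria and selected on six, and the sixth is a later outcome. A patient who is given acupuncture and dies in the ICU fails inclusion, so this death never enters the mortality analysis. The time from treatment start to ICU discharge is event-free by rule, yet the survival clock, which runs from admission, counts it as follow-up.

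If acupuncture changes who survives the ICU, the survivors in the two groups are no longer comparable. The same holds if the non-random grouping is related to ICU survival, which is plausible: section 2.7 gives edema and coagulopathy as examples of reasons for not giving acupuncture. At stake is a comparison that may show no effect, or one of the wrong sign, in a study whose second objective covers long-term prognosis and safety.

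The 7-day rule adds to this. It drops treated patients who qualify early and leave before day 7, and it truncates ICU length of stay, which is itself a secondary outcome.

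**Working it through.** **1. Order of events.** Inclusion 5 requires a fall in RF_CSA of more than 9.24%. Section 2.8.1 schedules scans on days 1, 3, 5, 7, 10 and 14, so the first scan that can show a fall is on day 3.

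| Rule | When it can be judged | Relative to treatment start |
|---|---|---|
| Inclusion 1 to 5 | Day 3 scan at the earliest | Before; triggers assessment and grouping |
| Exclusion 10, stay under 7 days | Day 7 | After, if the patient qualifies on day 3 or 5; in effect already settled if on day 7, 10 or 14 |
| Inclusion 6, alive through the ICU stay | ICU discharge | After, for everyone who starts treatment in the ICU |

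**2. What the outcome can still capture.** A death in the index stay fails inclusion 6. A readmission requires a prior discharge. So no component of the outcome can occur before ICU discharge; both can occur afterwards, up to 1 year.

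**3. The plan's own figure.** The plan gives no mortality figure. Its sample size uses polyneuromyopathy incidence of 12.5% vs 39.3%. With unpooled variance, (1.9600 + 0.8416)² × (0.125 × 0.875 + 0.393 × 0.607) / 0.268² = 38.02, so 39 per group as stated; 39 / 0.80 = 48.75 gives 49 if 20% dropout is assumed. This reproduces, but the present point does not rest on it.

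**4. Size without shared frailty (all inputs assumed).** Let m be ICU mortality and q post-ICU mortality, with q equal in both groups. Total mortality = m + (1 − m)q; mortality among ICU survivors = q.

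| m, control / acupuncture | q | Total, control / acupuncture | True difference | Difference among survivors |
|---|---|---|---|---|
| 20% / 10% | 15% | 32.0% / 23.5% | 8.5 points | 0 |
| 20% / 10% | 25% | 40.0% / 32.5% | 7.5 points | 0 |
| 30% / 20% | 15% | 40.5% / 32.0% | 8.5 points | 0 |
| 30% / 20% | 25% | 47.5% / 40.0% | 7.5 points | 0 |
| 40% / 30% | 15% | 49.0% / 40.5% | 8.5 points | 0 |
| 40% / 30% | 25% | 55.0% / 47.5% | 7.5 points | 0 |

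**5. Size with shared frailty (all inputs assumed).** Half the patients are frail. ICU death is 10% in the others; in the frail it is 50% (control) or 30% (acupuncture). Post-ICU death is 40% in the frail and 10% in the others, in both groups.

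- Control: ICU deaths 0.5 × 0.5 + 0.5 × 0.1 = 0.30. Survivors 0.25 frail + 0.45 others = 0.70. Later deaths 0.25 × 0.4 + 0.45 × 0.1 = 0.145. Total 44.5%; among survivors 0.145 / 0.70 = 20.7%.
- Acupuncture: ICU deaths 0.5 × 0.3 + 0.5 × 0.1 = 0.20. Survivors 0.35 + 0.45 = 0.80. Later deaths 0.35 × 0.4 + 0.45 × 0.1 = 0.185. Total 38.5%; among survivors 0.185 / 0.80 = 23.1%.

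A 6-point benefit becomes an apparent harm of 2.4 points. Changing ICU death in the frail (control / acupuncture) gives:

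- 40% / 20%: total 41.5% vs 35.5%; survivors 22.0% vs 24.1%.
- 60% / 40%: total 47.5% vs 41.5%; survivors 19.2% vs 22.0%.
- 40% / 40%, no ICU effect: total 41.5% vs 41.5%; survivors 22.0% vs 22.0%, so no bias.

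**6. Deaths left out.** If the 49 per group are ICU survivors and ICU mortality is the same in both groups at 10%, 20%, 30% or 40%, then 49 / (1 − m), rounded up, means starting 55, 62, 70 or 82 per group. In total, 12, 26, 42 or 66 deaths would be left out.

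**The case against.** Inclusion 6 applies to both groups. If acupuncture does not affect ICU survival, and the grouping is unrelated to it, the rule creates no difference, as the no-effect case above shows. A survivor population may be partly intended: section 2.8.4 speaks of sepsis survivors, and readmission exists only after discharge. The eligibility summary at the end of section 2.4.4 omits inclusion 6 and the 7-day rule, and the flowchart is not shown. These points stand as limits. They do not rescue the plan: a post-discharge question would need its clock at ICU discharge, not admission, and even then would not give the effect from treatment start.

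Four stronger readings are tempting, and the documents do not support them:

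- *The whole mortality outcome is conditioned on itself.* Only its in-ICU part is removed; later deaths and readmissions count.
- *All the late rules are judged after treatment starts.* The 7-day rule is so only for patients who qualify before day 7. The therapy in exclusion 12 is undefined: it may mean study treatment or life-sustaining care, and consent refusal can come before treatment.
- *Section 2.13 removes deteriorating patients from the acupuncture group only.* The events listed there are needle events, but the trigger is a change in condition that affects the study treatment plan, and controls also have prescribed exercises. The section does not say that withdrawn patients' data leave the analysis.
- *All three primary outcomes are shown to be biased.* RF_CSA and MRC-SS are also compared only among ICU survivors, but no size can be given for them, and both are unobserved after death under any eligibility rule.

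**Conclusion.** The point holds and must be fixed, because a primary outcome cannot be read as the effect of acupuncture on mortality while inclusion 6 defines who is in the study. This follows from the text alone: treatment and grouping on criteria 1 to 5, selection on survival to ICU discharge, and a mortality clock from admission. Exclusion 10 contributes for patients who qualify on the day 3 or day 5 scan. Covariate or propensity adjustment deals with baseline differences and cannot restore patients removed because of a later event.

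The direction and size are not known. The 7.5 to 8.5 points lost, and the reversal under frailty, depend on an assumed ICU mortality benefit of 10 points; the reversal also needs frailty that drives death both in and after the ICU. They show what the rule can do, not what it will do in this study.

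**What to change.** - Remove inclusion 6 and exclusion 10 as conditions for being in the analysis. Fix the cohort and time zero at the moment criteria 1 to 5 are met and the group is set, recorded in the same way for both groups.
- Start the Kaplan-Meier and Cox clock at time zero, count ICU deaths as events, and analyse by initial group.
- Report RF_CSA and MRC-SS alongside mortality, since neither can be observed after death. Keep an ICU-survivor analysis as a labelled secondary analysis.
- Define the therapy in exclusion 12. State there and in section 2.13 that patients whose study treatment stops remain in follow-up and analysis unless consent is withdrawn. The clinical decision to stop is not affected.
- Reconcile sections 2.4.3, 2.4.4, 2.5.1 and 2.8.6 so that they describe one study population.

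The cost is a protocol amendment, and outcome recording for ICU deaths and short stayers, whom section 2.4.1 already enters in the EDC system as sepsis patients. Some RF_CSA and MRC-SS values will be truncated by death, and the report must say so.
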